### Sample recruitment procedures

A range of recruitment strategies will be used to recruit participants. Investigators will work closely with the doctors as well as the nurses at the study sites to promote and identify participants diagnosed with type 2 diabetes. Participants may also be self-referred or referred through their primary care doctors.

Selection criteria include people: (1) with type 2 diabetes based on diagnosis by a doctor, for at least 6 months prior to study enrolment, determined via self-report with verification (medical records, current treatment); (2) aged 18–75 years; (3) residing in the state of Selangor without plans to leave for the next 12 months; (4) with HbA1c levels of ≥ 7.5 % but less than 11.0 % within the most recent 3 months; (5) who have regular access to internet and an e-mail address or access to a smartphone with 3G services. Participants will be excluded if they: (1) are unable or unwilling to give written informed consent or communicate with local study staff; (2) are currently diagnosed with mental disorder; (3) have been hospitalised for depression in the past six months; (4) do not have support from primary healthcare provider or family members; (5) are known to have history of bariatric surgery, small bowel resection, or extensive bowel resection, and (6) are currently pregnant or breastfeeding.

### Control arm

Participants in the control arm will be advised to continue their routine healthcare with their doctors, including self-management of blood glucose and recording of results in log books.

### Intervention arm

Participants in this arm will be encourage to self-monitor their blood glucose levels and will be provided with a group-based diabetes education, an automated feedback mechanism to both patient and family member(s) as well as an electronic logbook. The web-enabled function of the web-based glucose meter will be utilised, which when connected to an android enabled smartphone device, will automatically upload any blood glucose readings to an online portal which is currently managed by the Entra Health System. The web portal will host participant’s glycaemic and metabolic results as well as other information such as self-management skills, compliance to eye measurements and screening for microvascular complications. The system will be calibrated to generate a message to inform the attending doctor or researcher in the event that three consecutive readings of hypoglycaemia (3.9 mmol/L or below) or hyperglycaemia (11.1 mmol/L and above) are detected. A schematic diagram representing the elements of this system is shown in Fig. 2. The doctor or researcher will have the option to use this information to initiate an intervention. The doctor will be responsible for all treatment decisions. Participants in the intervention arm will receive monthly communications from the research team. Communications will focus on self-management skills, blood glucose control, and medication adherence. Figure 3 shows the process of the study trial.

**Fig. 3 Fig3:**
[figure not shown]
Schematic diagram of study trial process

### Focus group

To better understand participants’ perception towards this research, focus group sessions will be conducted. Interested participants will be given an overview of the purpose of the focus group discussion to ascertain their interest in participating in this discussion. These sessions will last between one and a half to two hours, and each session will consist of not more than eight participants, who will engage in discussion on the topics under consideration. Selection of participants will be based on common characteristics among them. A semi-structured interview protocol using open-ended questions to encourage group discussion, will be used and a trained moderator will conduct the focus group sessions. The moderator will provide nondirective, supportive and non-evaluative role. He/she is also responsible to facilitate participants’ responses and to prevent deviation from the topics being discussed. It is estimated that a total of five focus groups will be required to achieve saturation. Focus group sessions will be held at the times convenient to the participants. Interviews with the various healthcare professionals, including doctors and nurses, will be conducted to understand their opinion and acceptability in adapting telemonitoring into current Malaysian healthcare settings.

### Measurements

Table 1 details the measures that will be assessed throughout the study. HbA1c will be analysed using venous samples by ion-exchange high performance liquid chromatography (Cobas Integra 800, Roche), and serum lipids using enzymatic techniques (Advia 2400, Siemens). All blood specimens will be collected and analysed in a central laboratory operated by Gribbles Pathology, Malaysia to reduce variability.

**Table 1 Tab1:** Primary and secondary outcome measures for visit 0, 4, 12, 24, 52

Variable	Instrument
Primary outcome variable	
Glycaemic control	HbA1c
Secondary outcome variable	
Glycaemic control	Fasting plasma glucose
Blood lipids	Total cholesterol, LDL cholesterol, HDL cholesterol, triglycerides
Kidney function	Creatinine
Blood pressure	Measured twice using A&D UA-767 Plus BT-C blood pressure device on the same arm.
Blood oxygen saturation and pulse rate	Spo2; using Nonin Oximeter II Model 9560 on the right index finger.
Body Mass Index (BMI)	Calculated from height and weight measured by research staff.
Self-efficacy	Self-efficacy scale [46]
Diabetes distress	Diabetes distress scale [37]
Diabetes self-care	Diabetes self-care activities questionnaire [38]
Quality of life	EQ-5D [40]
Healthcare utilization	Self-reported using healthcare utilization questionnaire [39]
Smoking	Self-reported
Co-morbidities	Self-reported

*LDL* low density lipoprotein, *HDL* high density lipoprotein

Participants’ blood pressure will be calculated using the mean of two measurements performed with participants seated after at least 10 min rest, with the cuff on the predominant arm at the level of the heart (A&D, UA-767, USA). Body height and weight will be measured in light indoor clothing and without shoes using a stadiometer and a scale (A&D, UC-321 PBT-C, USA), respectively. Blood oxygen saturation and pulse rate will be measured using an oximeter (Nonin Oximeter II, Model 9560, USA).

Several generic and disease-specific instruments will be used in the current study to measure participants’ diabetes knowledge, quality of life, self-efficacy, diabetes distress and health care utilization. These include the diabetes distress scale [37], diabetes self-care activities [38], health care utilization [39] and EuroQol-5D (EQ-5D) [40]. Questionnaires will also be translated to Bahasa Malaysia and Mandarin if required, and subsequently validated.

### Data analysis

#### Data quality

A unique study identifier will be used to tag all study forms and biological samples which are collected during this study. Quantitative data will be entered into a database and audited for accuracy. In order to maintain participant confidentiality, coded form will be kept separately from the code list. Any missing and outlier values will be screened by a research assistant and hence, extensive training of research assistants is important to ensure quality of data entry.

#### Quantitative data analysis

Analysis of quantitative study data across randomised groups will be conducted in IBM SPSS version 20 (Armonk, NY). Continuous variables will be tested for normality and data, which are not normally distributed, will be analysed using Kruskal-Wallis and Wilcoxon signed ranks test. In the event of missing data, the last observation carry forward method will be used. A *p* value of < 0.05 will be considered as statistically significant for all the tests.

Effectiveness of the research intervention will be measured in terms of differences between study arms with respect to changes in biomedical measures and activities. Logistic regression will be used and both adjusted and unadjusted models will be presented. Benefits, barriers, confidence and knowledge will be included in a model to identify factors associated with the concept of intensive treatment and hypoglycaemia. An adjusted *t*-test using multiple linear regression analysis will be conducted to calculate variables for benefits, barriers and knowledge.

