### Randomisation

The study will follow a cluster randomised design with the public clinics as the unit of randomisation. This will avoid potential contamination between individuals who are assigned to different treatment groups in the same study site. A trained individual, independent of the study team will conduct all the randomisation.

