### Sample size calculation

A previous study in a tertiary hospital reported a 0.79 % mean difference in HbA1c between adherent and non-adherent people with diabetes [36]. A sample size of 100 people per study arm will have an 80 % power to detect a 0.5 % difference in HbA1c between the intervention and control arm. Therefore, after accounting for a 20 % loss to follow-up in each arm, 240 people with diabetes will be recruited in this study.

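### Clinics are randomised, but every named analysis treats participants as independent, so the 5% error rate is not held unless the intra-clinic correlation is zero

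*Protocol article*

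**What the plan says.** The Randomisation section of the protocol article fixes the unit: "The study will follow a cluster randomised design with the public clinics as the unit of randomisation".

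The Quantitative data analysis section sets the effect measure: "Effectiveness of the research intervention will be measured in terms of differences between study arms with respect to changes in biomedical measures and activities". It then names the methods:

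- For continuous variables that fail a normality check: "data, which are not normally distributed, will be analysed using Kruskal-Wallis and Wilcoxon signed ranks test".
- "Logistic regression will be used and both adjusted and unadjusted models will be presented".
- An adjusted t-test "using multiple linear regression analysis will be conducted to calculate variables for benefits, barriers and knowledge".
- One threshold throughout: a p "value of < 0.05 will be considered as statistically significant for all the tests".

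The article mentions no mixed model, generalised estimating equation (GEE), cluster-robust variance, clinic-level summary, ICC or design effect. The Sample size calculation section is also written for individuals: "A sample size of 100 people per study arm will have an 80 % power to detect a 0.5 % difference in HbA1c".

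**The concern.** Patients at one clinic are likely to share doctors, nurses and routines. The article itself has clinic staff helping to recruit, doctors making all treatment decisions and group-based education in the intervention arm. Some within-clinic correlation should therefore be expected. Because whole clinics are allocated, between-clinic variation feeds directly into the difference between arms.

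A method that ignores this uses a variance that is too small. In the regressions it appears as understated standard errors, and in the rank tests as a null variance that is too small. Either way the error runs towards false positives. It affects any between-arm comparison made with these methods, including HbA1c, and the article says the results are meant to inform policy makers.

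**Working it through.** **Inputs from the article.** Clinic is the randomised unit. There are 100 participants per arm for analysis, 80% power, a 0.5-point HbA1c difference, 20% loss and 240 recruited. The significance level is 0.05, taken as two-sided because sidedness is not stated.

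**Inputs assumed.** The article gives no clinic count or ICC for the main trial. The range used is K = 3 to 20 equal-sized clinics per arm and ICC 0.01 to 0.10. The only count reported is five centres in total, for the exploratory phase.

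**The plan's own figures.** No SD is given, so the 100 per arm can only be back-solved:

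SD = 0.5 / [(1.960 + 0.842) × √(2/100)] = 1.26.

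The total is 200 × 1.2 = 240. The dropout allowance accounts for all of the increase over 200, so no factor for clustering is included.

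**True error of an individual-level test.** With m = 100/K participants per clinic:

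- Design effect: DE = 1 + (m − 1) × ICC.
- True standard error = naive standard error × √DE.
- True two-sided error = 2 × [1 − Φ(1.96/√DE)].

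For K = 5 and ICC 0.05: m = 20, DE = 1 + 19 × 0.05 = 1.95, √DE = 1.40, and 2 × [1 − Φ(1.96/1.40)] ≈ 16.0%.

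| Clinics per arm | m | ICC 0.01 | ICC 0.05 | ICC 0.10 |
|---|---|---|---|---|
| 3 | 33.3 | 8.8% | 22.6% | 34.1% |
| 5 | 20 | 7.2% | 16.0% | 25.0% |
| 10 | 10 | 6.0% | 10.4% | 15.5% |
| 20 | 5 | 5.5% | 7.4% | 9.8% |

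Over this range the true standard error is 1.02 to 2.06 times the naive one.

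**Simulation check.** 4,000 null trials were run per setting, with normally distributed outcomes:

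| Clinics per arm | ICC | Kruskal-Wallis | t-test / linear regression | t-test on clinic means |
|---|---|---|---|---|
| 5 | 0.05 | 16.0% | 16.9% | 5.1% |
| 5 | 0.10 | 25.3% | 25.7% | 4.9% |
| 10 | 0.05 | 10.0% | 9.9% | 4.9% |
| 10 | 0.10 | 14.8% | 15.6% | 5.2% |
| 20 | 0.05 | 7.6% | 7.7% | 5.4% |
| 20 | 0.10 | 9.2% | 9.4% | 4.6% |

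With ICC = 0 every method stayed near 5%. The signed-rank test within one arm was inflated in the same way (15.6% at 5 clinics and ICC 0.05). Logistic regression was not simulated, but the same variance argument applies to it.

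**Power once clustering is allowed for.** The effective size is 100/DE per arm, with SD 1.26 and a normal approximation. For K = 5 and ICC 0.05 it is 100/1.95 = 51.3 per arm, which gives 52% power.

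| Clinics per arm | ICC 0.01 | ICC 0.05 | ICC 0.10 |
|---|---|---|---|
| 5 | 73% | 52% | 38% |
| 10 | 77% | 64% | 53% |
| 20 | 78% | 73% | 66% |

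These are somewhat optimistic because they apply no small-sample degrees of freedom.

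**The case against.** **No test is assigned to HbA1c by name.** The rank tests apply only to non-normal data, the linear regression is attached to the belief and knowledge variables, and logistic regression is attached to no outcome. If HbA1c change is normally distributed, the gap could be called detail left to a fuller document. It is true that no primary model is stated. But the section defines effectiveness as between-arm differences in biomedical change, lists its methods down to software version and threshold, and every method listed ignores clinic. That is a stated analysis that does not fit the design.

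**Adjustment might include clinic.** Nothing says so; the only model terms listed are belief, confidence and knowledge variables. Clinic as an ordinary fixed effect would not help either, since arm cannot be separated from clinic when whole clinics are randomised. The unadjusted models would leave clinic out in any case.

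**Some of the criticism does not apply literally.** The signed-rank test is a before-after test and makes no comparison of arms. One of the models is exploratory and is not stated to be an arm contrast. The section mentions no confidence intervals, so the claim there is only that any interval from these models would be too narrow. These points stand and narrow the wording.

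**The inflation may be small.** With many small clinics and a low ICC it is: 5.5% at 20 per arm and ICC 0.01. No ICC for HbA1c change is given, and the central laboratory removes one source of between-clinic variation. This stands as a limit on the size.

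**Conclusion.** The concern holds. The trial randomises clinics, and the analysis it names, in standard form, assumes independent participants. The direction is certain for any ICC above zero: too many false positives.

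The size is conditional. Over 3 to 20 equal-sized clinics per arm and ICC 0.01 to 0.10, the true error of a nominal 5% test runs from about 5.5% to about 34%. It is about 16% at 5 clinics per arm and ICC 0.05. Clinic count and ICC are assumptions, because the article states neither.

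This must be corrected before the final analysis, since it bears on the primary comparison.

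**What to change.** In the Quantitative data analysis section, name one primary analysis for HbA1c:

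- A linear mixed model with baseline HbA1c as a covariate, a random clinic intercept and small-sample degrees of freedom (Satterthwaite or Kenward-Roger).
- If clinics are few, instead a t-test on baseline-adjusted clinic means, with degrees of freedom equal to the number of clinics minus 2.

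The number of clinics is known without looking at outcomes. The choice between the two should therefore be written down, with its reason, before outcome data are analysed by arm. The visit that carries the primary comparison should be named as well, since Table 1 lists several.

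For binary outcomes, use the mixed or GEE counterpart with a small-sample correction. For markedly non-normal outcomes, use a clinic-level analysis in place of Kruskal-Wallis. Do not use the signed-rank test as evidence of a difference between arms. State the number of clinics per arm and report the estimated ICC.

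**Cost.** The change needs revised text and modest extra programming. No new data are needed, because clinic is known for every participant. Intervals will be wider and power lower than planned: with 5 clinics per arm, about 73%, 52% or 38% at ICC 0.01, 0.05 or 0.10, against the stated 80%. The present analysis hides that shortfall; the correction does not create it.

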### Outcome measures

The primary outcome of this study is changes in HbA1c levels pre and post intervention. Secondary outcome measures include changes in body weight, fasting blood glucose, blood pressure, quality of life and physical activity.

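### Last observation carried forward is the only stated rule for missing data; with 20% loss expected in each arm, it can bias the HbA1c comparison even if loss is completely random

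*Protocol article*

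**What the plan says.** The protocol article, under Quantitative data analysis, gives a single instruction: "In the event of missing data, the last observation carry forward method will be used". It is not restricted to any variable, visit or reason for missingness, and the article names no other method. The Data quality section adds only that a research assistant will screen missing and outlying values.

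The rule reaches the primary outcome. Outcome measures states: "The primary outcome of this study is changes in HbA1c levels pre and post intervention". Table 1 lists HbA1c under a title naming visits 0, 4, 12, 24 and 52 (unit not printed).

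Sample size calculation expects substantial loss: "after accounting for a 20 % loss to follow-up in each arm, 240 people with diabetes will be recruited in this study". The trial is sized "to detect a 0.5 % difference in HbA1c between the intervention and control arm".

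**The concern.** Carrying a value forward sets the final HbA1c of a lost participant equal to the last one seen. Someone lost after visit 0 then enters with zero change, and someone lost later enters with an intermediate change. The mean at the final visit is right only if HbA1c stops moving after dropout or if the errors cancel.

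A trial designed to find a 0.5 difference expects means to move in at least one arm. The section on relevance to public health also wants to learn whether the effect lasts, whereas this rule assumes that it does for every participant who leaves. At stake is the primary treatment estimate, which could be diluted, inflated or, with unequal loss, shifted from zero when nothing happened.

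**Working it through.** **Inputs from the article.** 240 recruited = 200 x 1.2, so 120 per arm. Loss of 20% is 0.20 x 120 = 24 per arm, 48 in all. Planned effect 0.5. Visits 0, 4, 12, 24, 52.

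**Assumed inputs (not in the article).** Visit 52 is the final value, visit 0 may be carried forward, and loss is unrelated to HbA1c. Mean changes from baseline at the five visits:

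- control: 0, -0.2, -0.5, -0.6, -0.6
- effect: 0, -0.1, -0.4, -0.5, -0.5
- intervention (the sum): 0, -0.3, -0.9, -1.1, -1.1

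**Formula.** Expected mean change in an arm = sum over visits of (share whose last value is at that visit) x (mean change there). The contrast is intervention minus control; the truth is -0.50.

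1. Equal 20% loss, 5% last seen at each of visits 0, 4, 12, 24: 0.80 x (-0.5) + 0.05 x (0 - 0.1 - 0.4 - 0.5) = -0.40 - 0.05 = **-0.45**.
2. Equal 20% loss, 10% last seen at visit 0 and 10% at visit 4: -0.40 + 0.10 x (0 - 0.1) = **-0.41**.
3. Loss 30% intervention, 10% control, spread evenly (7.5% and 2.5% per visit). Intervention: 0.70 x (-1.1) + 0.075 x (-2.3) = -0.9425. Control: 0.90 x (-0.6) + 0.025 x (-1.3) = -0.5725. Contrast **-0.37**.
4. The reverse, 10% and 30%. Intervention: 0.90 x (-1.1) + 0.025 x (-2.3) = -1.0475. Control: 0.70 x (-0.6) + 0.075 x (-1.3) = -0.5175. Contrast **-0.53**.
5. No true effect (both arms on the control course), 30% intervention and 10% control: -0.5175 - (-0.5725) = **+0.055**.
6. No true effect, equal loss in the same pattern: the two sums are identical, contrast **0**.

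**Other assumed courses**, with a flat control arm and equal, evenly spread 20% loss:

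- Effect 0, -0.3, -0.7, -0.8, -0.5: -0.40 + 0.05 x (-1.8) = -0.49, close to the true -0.50.
- Effect 0, -0.4, -0.7, -0.6, 0 (gone by the last visit): 0 + 0.05 x (-1.7) = -0.085, where the truth is 0.

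The sign and size therefore follow the assumed course and dropout pattern.

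**Standard error.** The article gives no SD. 100 per arm, 80% power and two-sided 0.05 imply 0.5 / ((1.960 + 0.842) x sqrt(2/100)) = 1.26. Simulation with this SD, 120 per arm, an assumed within-person correlation of 0.5, even random 20% loss, the control course above and no clustering gave:

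| | Reported SE | Actual sampling SD | Coverage |
|---|---|---|---|
| No effect | 0.160 | 0.158 | 95.4% |
| With the effect above | 0.161 | 0.162 | 93.7% |

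The reported standard error agrees with the real variability of the carried-forward estimate. The slight loss of coverage in the second row comes from the bias in step 1.

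**The case against.** The strongest reply is that the effect is modest under the plan's own expectation. The article plans the same loss in both arms: "after accounting for a 20 % loss to follow-up in each arm". With equal, evenly spread loss the main illustration is off by 0.05, toward no difference, or about 0.05 / 0.16 = 0.3 of a standard error. The 30% and 10% split has no source in the article, and neither have the assumed courses. All of this stands. It is why no size or direction can be asserted, and why the point falls short of a fatal flaw. It does not rescue the rule, because equal loss gives no protection when an effect builds or fades over time.

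An analysis plan that is not shown may contain sensitivity analyses. That is possible, so their absence is not held against the article. The point concerns the method that the article itself fixes.

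Two stronger readings are tempting but unsupported:

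- A reader might infer that treating carried values as real makes the standard errors too small. Each carried value is a function of that person's own observed data, so the ordinary two-sample formula estimates its variance correctly, and the simulation agrees. A comparable run shows 0.159 for carried-forward values against 0.182 for observed final values, but these are two different estimators using different numbers of people.
- A reader might infer that entry at 7.5% or above makes baseline values systematically high, so that carried baselines must be too high. Eligibility rests on an HbA1c "within the most recent 3 months", while Table 1 lists a visit-0 value. If that is a fresh sample, part of any regression to the mean occurs before baseline.

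**Conclusion.** The concern holds as a liability to bias, and the rule should be changed. As written, the plan applies carrying forward to the primary outcome with about 48 of 240 participants expected to be lost. The between-arm HbA1c difference can then be wrong even under completely random loss, whenever means move over time or loss differs by arm.

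Under the main assumed course, the estimate runs from -0.37 to -0.53 against a true -0.50. A spurious +0.055 appears with unequal loss and no effect, and nothing appears with equal loss and no effect. These figures illustrate; the article does not supply the courses, the dropout timing or any imbalance between arms. Loss related to HbA1c itself was not examined. The conclusion does not rest on understated standard errors or on high baseline selection.

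**What to change.** In Quantitative data analysis, replace carrying forward as the primary approach with a likelihood-based linear mixed model for HbA1c using all scheduled visits, with baseline, arm-by-visit terms and a random clinic effect. The between-arm contrast at a named final visit is the primary estimate. This uses every observed value and is valid under missing at random.

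For outcomes that need complete data, use multiple imputation that respects clinics. Keep carrying forward at most as a sensitivity analysis. A delta-shift analysis for data not missing at random would be a useful option, but the correction does not depend on it.

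The cost is plan wording and modest programming. The visits are already scheduled, so no new data are needed.

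### The primary effect is an arm difference in HbA1c change, and no adjustment of that comparison for the HbA1c measured at visit 0 is specified

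*Protocol article*

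**What the plan says.** Outcome measures gives the endpoint: "The primary outcome of this study is changes in HbA1c levels pre and post intervention". Quantitative data analysis gives the effect measure: "Effectiveness of the research intervention will be measured in terms of differences between study arms with respect to changes in biomedical measures and activities". The modelling sentence that follows is "Logistic regression will be used and both adjusted and unadjusted models will be presented". It lists no covariates and does not say which version is primary.

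The only linear regression in the section is for other variables: "An adjusted *t*-test using multiple linear regression analysis will be conducted to calculate variables for benefits, barriers and knowledge". For continuous data that are not normal, the section names the Kruskal-Wallis and Wilcoxon signed-rank tests.

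The baseline value is available. Table 1 in Measurements is headed "Primary and secondary outcome measures for visit 0, 4, 12, 24, 52" and lists HbA1c as the primary variable. On allocation, the Randomisation section says: "The study will follow a cluster randomised design with the public clinics as the unit of randomisation".

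**The concern.** A plain comparison of change scores fixes the slope of follow-up on baseline HbA1c at 1. Sample recruitment procedures admits patients on a raised HbA1c (7.5% to below 11.0%), where some regression to the mean is expected, so a slope below 1 is likely. Two things follow if baseline is not a covariate.

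- **Precision.** The change score carries baseline variation that a fitted slope would remove, so power is lost for the same patients.
- **Chance imbalance.** If one arm's clinics start higher, that arm tends to fall further without any treatment effect. Subtracting baseline does not fully correct for this when the slope is below 1. Randomising clinics makes a difference in mean baseline more likely than randomising individuals does.

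The target difference is 0.5 HbA1c points, so a residual of around a tenth of a point would be noticeable. The issue is separate from the choice of logistic regression: a linear test of change that allowed for clinic would still have it if visit-0 HbA1c were left out.

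**Working it through.** **1. Is baseline adjustment of the HbA1c comparison stated anywhere?**

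| Method named in Quantitative data analysis | Applies to | Uses visit-0 HbA1c? |
|---|---|---|
| Arm difference in change | Biomedical measures, so HbA1c | Only by subtraction |
| Logistic regression, adjusted and unadjusted | Outcome not stated | Covariates unnamed; does not estimate a mean HbA1c difference |
| Kruskal-Wallis, Wilcoxon signed-rank | Non-normal continuous data | Neither takes a covariate |
| Multiple linear regression | Benefits, barriers, knowledge | Not an HbA1c analysis |

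It is not stated, and it is not ruled out either.

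**2. The plan's own figure.** Sample size calculation states: "A sample size of 100 people per study arm will have an 80 % power to detect a 0.5 % difference in HbA1c". No SD is given, so I solve for it, taking alpha 0.05 as two-sided (the sidedness is not stated) and using the normal approximation:

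SD = 0.5 / [(1.960 + 0.842) × √(2/100)] = 0.5 / 0.396 = 1.26.

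This returns 100 per arm and 80% power. A one-sided test would imply 1.42. Whether 1.26 is the SD of change or of the HbA1c level is not stated. I read it first as the SD of change.

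**3. Precision.** With follow-up = a + b × baseline + residual:

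- Var(change) = Var(residual) + SD_baseline² × (1 - b)²
- Variance ratio, adjusted to unadjusted = 1 - SD_baseline² × (1 - b)² / SD_change²

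Here SD_change² = 1.262² = 1.593. The baseline SD is assumed. A uniform spread over 7.5 to 11.0 has SD 3.5/√12 = 1.01, so 1.0 is a generous value and 0.8 a narrower one. Power = Φ(2.802/√ratio - 1.960).

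| Baseline SD | Slope b | Ratio | Power unadjusted | Power adjusted |
|---|---|---|---|---|
| 1.0 | 0.5 | 1 - 0.250/1.593 = 0.843 | 80% | 86% |
| 1.0 | 0.7 | 1 - 0.090/1.593 = 0.943 | 80% | 82% |
| 0.8 | 0.5 | 1 - 0.160/1.593 = 0.900 | 80% | 84% |
| 0.8 | 0.7 | 1 - 0.058/1.593 = 0.964 | 80% | 81% |

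If 1.26 is instead the SD of follow-up HbA1c, with baseline SD 1.0, then Var(residual) = 1.593 - b². At b = 0.5 this is 1.343 and Var(change) is 1.593, so power again goes from 80% to 86%. At b = 0.7 they are 1.103 and 1.193, and power goes from 90% to 92%.

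All these figures are at the individual level. The article gives neither the number of clinics nor an intracluster correlation, so a clustered version cannot be computed from it.

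**4. Residual imbalance.** For a baseline difference d, the change comparison is shifted by d × (1 - b). With d = 0.2 (assumed):

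- b = 0.5: 0.2 × 0.5 = 0.10 points, 20% of the 0.5 target.
- b = 0.7: 0.2 × 0.3 = 0.06 points, 12% of the target.

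To judge d, assume baseline SD 1.0, 120 recruited per arm, 4 clinics of 30 per arm and intracluster correlation 0.05. The SD of the chance difference is then √[2 × (1 + 29 × 0.05)/120] = 0.20. Individual randomisation would give √(2/120) = 0.13.

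**The case against.** The strongest reply is that the article promises adjusted models. Visit-0 HbA1c may be among their covariates, and an article commonly leaves a covariate list to the full protocol or analysis plan. Nor does a change outcome exclude adjustment: regressing change on arm and baseline gives the same treatment effect as regressing follow-up on arm and baseline. Both points stand. A reader might infer that the plan rules adjustment out, but the text does not say so. What remains is that the adjusted model named is logistic, and baseline in that model would not adjust a mean HbA1c comparison.

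A reader might also apply the usual equal-variance formula, ratio (1 + r)/2, and claim a rise from 80% to 90% at r = 0.5. The eligibility range argues against this. With an SD of change of 1.26, equal variances need a baseline SD of 1.26/√(2(1 - r)): 1.26 at r = 0.5, 1.63 at 0.7 and 1.99 at 0.8. Values confined to a 3.5-point range cannot exceed an SD of 1.75, and a single-peaked distribution cannot exceed 3.5/3 = 1.17. Eligibility may use a result up to 3 months old, so visit-0 values may spread somewhat wider, but not enough to make those figures the headline.

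A third tempting reading is that change scores are biased, or that they pass on the whole clinic imbalance. Under randomisation they are unbiased on average, and subtraction removes the slope's share of any imbalance. Stable differences between clinics may also have a slope near 1. In that case change scores correct them well and an individual-level covariate may correct them less fully. This limits the imbalance argument but does not affect the individual-level precision argument.

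**Conclusion.** The point holds in a limited form. The effect is defined on HbA1c change, and adjustment of that comparison for visit-0 HbA1c is not specified, although the value is collected. If the comparison is run unadjusted, it will generally be less precise than the adjusted one. It will also leave (1 - slope) times any chance baseline imbalance in the estimate.

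The likely gain is a few points of power: from 80% to about 86% at a slope of 0.5 and about 82% at 0.7. A 0.2-point imbalance would leave about 0.06 to 0.10 points. These sizes rest on an SD of change of 1.26 inferred from the sample size, an assumed baseline SD of about 1.0, assumed slopes and no clustering. The document fixes none of them. The point is a worthwhile improvement at almost no cost and does not show the planned analysis to be invalid.

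**What to change.** State in Quantitative data analysis that the primary HbA1c comparison is a linear model of follow-up HbA1c (or, equivalently, of change) on arm, with the individual's visit-0 HbA1c as a covariate, alongside the clinic term. Clinic should enter as a random effect or through a cluster-adjusted variance, because fixed clinic effects cannot be separated from arm when whole clinics are allocated. Name this as the primary estimate and report the unadjusted change as descriptive. Use the same form for the continuous secondary outcomes measured at visit 0.

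The cost is wording and one degree of freedom. No extra patients, visits or tests are needed.
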